### 2.14. Validity and Reliability/Rigour

The clinical trial offers guarantees in terms of internal validity, reducing possible bias and confounding variables. However, before data analysis, group homogeneity will be verified, and a multivariant analysis carried out to detect possible confounding and/or interaction variables.

Prior to starting the study, researchers will agree the data collection notebook and prepare instructions. Before collecting data, a pilot of the data collection notebook will be run to validate its content and the homogeneity of the data collected. A short video tutorial on data collection will also be collected.

### 2.15. Monitoring

An interim analysis is performed on the primary endpoint when 20% of patients have been randomized. The idea is to be able to identify an increase in HIV incidence in the control group, such as other potential hazard events in all participants. In that case, the study would come to a halt. The main investigator will have unblinded access to data and will discuss the results of the interim analysis with the research team.

The trial will not be stopped in case of futility related to the outcome variables because kangaroo care is the current intervention in the neonatal units due to clinically proven benefits, so futility is not sustainable.

The main investigator has the ultimate authority to stop or modify the trial and to ensure the protocol’s continued. He will follow up with all participants, and he will check all kangaroo care sessions are completed as it is referred to in the protocol. If that is not the case, the session will be discarded.

Changes on the protocol will be notified to all team members immediately and keeping all documentation standardized. All updated versions will be available in a digital form, and team members will be noticed during practical and theoretical lectures.

Safety and complications were monitored by identifying kangaroo potential adverse events noted down in the Data Collection Logbook (DCL), such as hypothermia, continuous hemodynamic instability during kangaroo care, or accidental displacement of any therapeutic device. Those events will be collected and analyzed in the first 24 h by the investigator in charge of the session, notifying the main investigator. The main investigator will record this adverse event on the study database, taking the actions required according to the severity and impact.

A committee in charge of data monitoring has not been created, the tracking is carried out by the research team. Non-audits have been scheduled.

Preliminary analyses every 20 new participants will be done to discard a rising HIV incidence in the control group, which would mean the study would come to a standstill.

Established withdrawal criteria are hypothermia or a Kangaroo care session less than 60 min.

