## Abstract

Introduction: This study aims to assess the efficacy of the modified kangaroo care lateral position on the thermal stability of preterm neonates versus conventional kangaroo care prone position. Material and methods: A non-inferiority randomized parallel clinical trial. Kangaroo care will be performed in a lateral position for the experimental group and in a prone position for the control group preterm. The study will take place at the neonatal intensive care unit (NICU) of a University Hospital. The participants will be extremely premature infants (under 28 weeks of gestational age) along the first five days of life, hemodynamically stable, with mother or father willing to do kangaroo care and give their written consent to participate in the study. The sample size calculated was 35 participants in each group. When the premature infant is hemodynamically stable and one of the parents stays in the NICU, the patient will be randomized into two groups: an experimental group or a control group. The primary outcome is premature infant axillary temperature. Neonatal pain level and intraventricular hemorrhage are secondary outcomes. Discussion: There is no scientific evidence on modified kangaroo care lateral position. Furthermore, there is little evidence of increased intraventricular hemorrhage association with the lateral head position necessary in conventional or prone kangaroo care in extremely premature newborns. Kangaroo care is a priority intervention in neonatal units increasing the time of use more and more, making postural changes necessary to optimize comfort and minimize risks with kangaroo care lateral position as an alternative to conventional prone position kangaroo care. Meanwhile, it is essential to ensure that the conventional kangaroo care prone position, which requires the head to lay sideways, is a safe position in terms of preventing intraventricular hemorrhage in the first five days of life of children under 28 weeks of gestational age. Trial registration at clinicaltrials.gov: NCT03990116.

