### 2.7. Blinding

Both clinicians/caregivers and research nurses will be informed of the group to which each participant is assigned due to their involvement in facilitating the care intervention for each group. However, non-caregiver researchers and those responsible for processing and analyzing the data will be blinded to assignment.

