### 2.12. Data Management

The data obtained from the participants will be included in an SPSS database (version 25) (IBM, Chicago, IL, USA). Data will be entered by the lead researcher, who will be the only person with access to the database.

Patients will be coded according to the order in which they join the study, following number allocation, through randomization.

Prior to statistical analysis, in order to improve the quality of data collected, the database will be debugged with the summarize function, identifying outliers, and the analysis of losses.

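### The interim plan in section 2.15 contradicts itself on endpoint and timing, orders a halt on an undefined rise in control-arm IVH, and conflicts with the analyst blinding in section 2.7

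*Protocol article*

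**What the plan says.** All of the interim plan is in section 2.15 of the protocol article.

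- **First statement.** "An interim analysis is performed on the primary endpoint when 20% of patients have been randomized". The aim that follows is to "identify an increase in HIV incidence in the control group, such as other potential hazard events in all participants", and the study then halts. HIV is an evident misprint for IVH.
- **Second statement, later in the section.** "Preliminary analyses every 20 new participants will be done to discard a rising HIV incidence in the control group", again with a standstill as the consequence.
- **Who sees the data.** "The main investigator will have unblinded access to data and will discuss the results of the interim analysis with the research team". The main investigator also holds final authority to stop. There is no data monitoring committee.

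Elsewhere, the Abstract says "The primary outcome is premature infant axillary temperature" and "Neonatal pain level and intraventricular hemorrhage are secondary outcomes"; section 2.10 agrees. Section 2.7 says that "those responsible for processing and analyzing the data will be blinded to assignment". Section 2.12 says: "Data will be entered by the lead researcher, who will be the only person with access to the database".

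**The concern.** A team following section 2.15 could not tell which variable to analyze, how many times, or what result ends the trial. Four things are at stake.

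- **Endpoint.** Read as written, the interim is an unblinded temperature comparison that its stated purpose does not need.
- **Number of looks.** The text allows one look, three or four.
- **Trigger.** Halting is presented as the consequence of a rise, with no comparator and no size. How often chance alone would end the trial depends on a choice made after the data are seen. An IVH excess in the lateral arm meets no stated IVH criterion.
- **Information flow.** Interim results reach the research team, which includes nurses who know the allocation. The Discussion concedes that the pain observers cannot be blinded. Knowing the emerging results could affect later handling and scoring.

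**Working it through.** **1. Endpoint.** The first statement names the primary endpoint, which is temperature (Abstract, 2.10). The purpose in the next sentence is IVH, which is secondary. Both cannot describe the same analysis.

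**2. Timing.** Section 2.6 numbers participants 1 to 70, so 20% is 0.20 × 70 = 14. Every 20 new participants gives 20, 40 and 60. The two could be additive (14/20/40/60), or the count could restart after the first look (14/34/54). The text does not say.

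**3. Trigger.** Both statements refer to a rise in the control group. Neither says compared with what (lateral arm, background rate or previous look), by how much, or by which test. Section 2.13 names chi-squared for IVH and p<0.05, but does not link them to the interim.

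**4. Illustration of what the gap allows.** The plan gives no stopping probability to reproduce.

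Inputs:
- IVH rate 20–38% under 28 weeks (Introduction), equal in both arms.
- Assumed 5–10% for new bleeds. Section 2.11 specifies a scan before the first session that separates earlier bleeds, but the documents give no rate of new bleeds.
- Allocation: equal arms at each look, or simple 1:1 as in section 2.6.

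Rule A: halt at the first look where control IVH exceeds lateral IVH. At a single look with equal arms, P = (1 − P(tie))/2. At a 20% rate this is 0.37 with 7 per arm and 0.39 with 10 per arm. Repeated looks were simulated with at least 100,000 trials per scenario.

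Rule B: halt when z = (p_C − p_L)/√[p(1−p)(1/n_C + 1/n_L)] > 1.96 at any look, where p_C and p_L are the observed control and lateral proportions and p is the pooled proportion.

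| Rule, with no true IVH effect | Looks 20/40/60 | Looks 14/20/40/60 |
|---|---|---|
| A, equal arms, IVH 20–38% | about 60–61% | about 63–65% |
| A, simple randomization, proportions compared, IVH 20–38% | about 67% | about 71–72% |
| A, equal arms, new IVH 5–10% (assumed) | about 49–56% | about 50–59% |
| B, equal arms, IVH 20–38% | about 5% | about 5–6% |
| B, equal arms, new IVH 5–10% (assumed) | about 2–4% | about 2–4% |

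**5. What a nominal criterion would detect.** For |z| > 1.96 at 20/40/60 with equal arms, the false-signal rate is up to about 5% per arm and up to about 10% in total. Detection is 46% for 40% vs 20%, 24% for 20% vs 10%, and 12% for 10% vs 5%. The look at 14 infants alone detects 40% vs 20% only about 10% of the time.

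**6. Blinding.** Section 2.7 blinds those who process and analyze data. Section 2.12 lets only the lead researcher into the database. Section 2.15 gives the main investigator unblinded data and has that person record adverse events in the database. If these two roles are one person, as the text suggests, nobody blinded can run the looks. If they are two people, sections 2.12 and 2.15 disagree on access.

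**The case against.** The strongest reply is that the defects are mostly drafting, and that heavier readings go beyond the text. Much of this stands.

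- A reader might infer that the trial would stop 60–65% of the time with no IVH effect. The documents do not support that as a finding. They never say that any numerical excess halts the trial. The figure also needs equal arms at each look and the overall IVH rate. The only significance level stated, p<0.05 in section 2.13, would give about 5%. Section 2.15 also has results discussed before anyone with authority acts, which suggests judgement.
- A reader might infer that the stop rule protects one arm only. That is too broad, because the first statement also covers other hazards in all participants. Only the named IVH trigger is specific to the control arm, and it follows the trial's hypothesis about the prone head turn.
- A reader might infer that the temperature look inflates type I error. No efficacy stop on temperature is stated and futility stopping is ruled out, so this does not follow. The objection to that look is that it is unnecessary and unblinded.
- A numerical boundary may sit in an analysis plan not shown here, so its absence alone would be weak ground.

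What the reply does not remove is the endpoint mismatch, the two timings, the halt tied to an undefined rise, and the conflict with section 2.7. These stand in the published text, and a separate plan would have to contradict part of that text to resolve them.

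**Conclusion.** The point holds and should be fixed. Section 2.15 names temperature where it means IVH, and gives two unreconciled timings for the same purpose. It orders a halt on a control-arm rise with no comparator or size and no counterpart for IVH in the lateral arm. It also passes unblinded interim results to the research team despite section 2.7.

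The endpoint and timing contradictions are certain from the text. The numbers show only how much is left open: with no IVH effect, about 5% under a nominal p<0.05 criterion in the control direction, and about 50–70% if any excess counts. The range depends on the trigger, the IVH rate (20–38% overall, 5–10% assumed for new bleeds) and arm balance. It is not a predicted stopping rate for this trial.

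**What to change.** Reconcile the two statements into one paragraph.

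- Delete the reference to the primary endpoint and the conflicting 20% timing. State one schedule of safety looks, for example at 20, 40 and 60 infants, on new or worsened IVH since the baseline scan, with no between-arm temperature comparison.
- State a numeric review guideline, chosen by the sponsor, that applies to an excess in either arm. Report its false-signal and detection rates at a plausible rate of new IVH. If the sponsor took two-sided nominal p<0.05 at each look, the rates in step 5 above would apply. The 46% detection rests on the overall IVH rate and should not be quoted for new bleeds.
- Have an existing non-caregiver researcher run the looks under coded arms and release only *continue* or *review* to the treating team. Amend the access rule in section 2.12 to allow this.
- Correct HIV to IVH.

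The cost is protocol wording, access for one more person and a declared false-signal probability, up to about 10% in total in the example. Detection will stay low at this sample size, and the text should say so.

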### 2.6. Randomization and Allocation

Participants will be recruited through non-probabilistic consecutive sampling.

Potentially eligible newborn patients will be identified in the research staff’s daily clinical practice or referred to them for eligibility assessment once they have been identified by clinicians who are not research staff.

Premature infants who meet all of the inclusion criteria and will be performing kangaroo care for the first time will be assigned to the experimental or control group on a simple 1:1 randomized basis, using a list of randomized numbers according to ID assignment from 1 to 70, using the random.org website.

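### Unblinded interim results, including a between-arm temperature comparison that no stated decision uses, are to be discussed with a research team that appears to overlap with enrolling and caring staff

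*Protocol article*

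**What the plan says.** Section 2.15 sets the timing and endpoint of the first look: "An interim analysis is performed on the primary endpoint when 20% of patients have been randomized". The next sentence gives its purpose: "The idea is to be able to identify an increase in HIV incidence in the control group, such as other potential hazard events in all" infants. 'HIV' there is evidently IVH. An adverse finding of that kind would halt the study. On who sees the results, the section says: "The main investigator will have unblinded access to data and will discuss the results of the interim analysis with the research team".

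The same section also states:
- "The trial will not be stopped in case of futility related to the outcome variables".
- "The main investigator has the ultimate authority to stop or modify the trial". This person also checks the sessions, and non-conforming sessions are discarded.
- "A committee in charge of data monitoring has not been created, the tracking is carried out by the research team".
- IVH is looked at again after every 20 new participants.
- Hypothermia is among the adverse events to be logged. Each event is analysed within 24 hours by the investigator in charge of the session.

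On roles, section 2.6 has research staff identifying candidates and assessing eligibility. Section 2.7 says: "Both clinicians/caregivers and research nurses will be informed of the group to which each participant is assigned", because they help deliver the care. It then says that non-caregiver researchers and those who process or analyse the data stay blinded. Section 2.12 gives the lead researcher sole access to the database.

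**The concern.** The trial is open-label and tests non-inferiority. Staff already know each infant's arm. The interim adds knowledge of how the arms compare so far. People who hold that knowledge can, without intending to, handle, cover or score later infants differently. An unblinded person who decides which sessions are discarded is a further route. In a non-inferiority trial, drift that makes the arms look alike favours a false claim.

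That exposure might be worth accepting if the look informed a decision. For the temperature comparison the protocol names none. Any later change to the outcome, margin or sample size by someone who had seen the running comparison would also be hard to defend.

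**Working it through.** **1. Infants recruited after the first disclosure.** Section 2.6 numbers participants 1 to 70.
- First look: 0.20 × 70 = 14 infants, about 7 per arm under simple 1:1 randomisation.
- Still to enter: 70 − 14 = 56, and 56/70 = 80%.

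**2. The plan's own sample size.** Section 2.5 gives SD 0.16 °C, margin 0.2 °C, difference 0.3 °C, power 80%, α 0.05 and 10% loss.
- With a distance of 0.3 − 0.2 = 0.1 °C and one-sided α of 0.05: n = 2 × (1.645 + 0.842)² × 0.16² / 0.1² = 31.7, so 32 per arm.
- With 10% loss: 32/0.9 = 35.6, so 36. This is within one of the stated 35.
- The SD and the total of 70 are therefore usable below.

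**3. What the temperature look would show.**
- SE = 0.16 × √(2/7) = 0.0855 °C.
- 95% half-width with t on 12 degrees of freedom: 2.179 × 0.0855 = 0.186 °C. The normal approximation gives 1.96 × 0.0855 = 0.168 °C.
- Margin: 0.2 °C.
- With no true difference, the chance that lateral appears at least 0.1 °C colder is Φ(−0.1/0.0855) = 12%.

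The team would mostly be told noise, on a scale large enough to leave an impression.

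**4. Whether any rule uses the comparison (section 2.15).**

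| Possible use | What the protocol states |
|---|---|
| Stop for efficacy or non-inferiority | No rule given |
| Stop for futility | Excluded for the outcome variables |
| Halt for IVH | Yes, but this needs IVH counts |
| Halt for other hazards | Yes; hypothermia could count, but it is already logged as an adverse event |

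The last two rows need counts of events. None needs a between-arm comparison of mean temperature.

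**5. Who would hear the results.**
- Section 2.6: research staff assess eligibility.
- Section 2.7: research nurses know the arm and help deliver the care.
- Section 2.15: the research team does the tracking, and an investigator is in charge of each session.
- Table 1: the neonatal nurse carries out the positioning and records temperature and pain.
- Section 2.8 does not say who adds or removes covers.

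Overlap with enrolment, care and session conduct is well supported. Complete overlap is not.

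**6. Illustration only (the bias is assumed).** Take 31 evaluable per arm (35 × 0.9 = 31.5), so SE = 0.16 × √(2/31) = 0.0406 °C. Suppose the true difference lies at the margin and the test is one-sided at 2.5%. The non-central t distribution on 60 degrees of freedom gives:

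| Net bias assumed | False non-inferiority |
|---|---|
| 0.04 °C away from equality | 0.2% |
| none | 2.5% |
| 0.01 °C towards equality | 4.3% |
| 0.02 °C towards equality | 7.0% |
| 0.03 °C towards equality | 10.9% |
| 0.04 °C towards equality | 16.1% |

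A net 0.04 °C corresponds to a 0.05 °C shift in the later 80% (0.8 × 0.05). At one-sided 5%, the level that reproduces the plan's n, that shift takes the rate from 5% to 25%.

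**The case against.** Several counter-arguments have weight.

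- **Team membership is inferred.** A reader might conclude that the results go to exactly the people who enrol, position, cover and score. The documents do not say so: the team is not listed, and Table 1 gives positioning, temperature and pain to the neonatal nurse. This stands, and the point is limited to overlap.
- **The endpoint may be a slip.** The stated purpose is IVH and hazards, so the words naming the primary endpoint may be a mistake. If so, the temperature part falls away, but the sentence on discussing unblinded results remains. As printed, the look is on the primary endpoint.
- **Hypothermia could be a hazard that halts the trial.** True, so it is too strong to say that temperature data have no safety use. Adverse-event counts meet that need.
- **The routes to bias are limited.** Knowing the running difference does not reveal the next allocation. Cover changes follow written temperature triggers, and temperature is measured by probe. Unblinded pain scoring exists without any interim and is a declared limitation. These points reduce the likely bias but do not remove it.
- **The main investigator may see by-arm data anyway.** If the main investigator is also the lead researcher of section 2.12, restricting the interim does not blind that person. This stands. It also means that a blinded non-caregiver researcher could not hold the counts without changing sections 2.7 and 2.12.

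**Conclusion.** The point holds in a limited form. Section 2.15 states a procedure that circulates unblinded interim results, on its face including the primary outcome, within a research team that very probably includes people who recruit and look after later infants. It conflicts with the blinding promised in section 2.7. The between-arm temperature comparison supports no stated decision.

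The exposure covers 56 of 70 infants (80%). The look behind it has a 95% half-width of 0.19 °C against a 0.2 °C margin, assuming 7 per arm and the planned SD of 0.16 °C.

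A reader might infer from the illustration that the false non-inferiority rate becomes 16%. The documents do not support that. The shift is assumed, and the same calculation runs from 0.2% to 16.1% according to its size and direction. The case for change rests on avoidable exposure with no matching benefit. The change should be made, but the protocol does not show that the trial's result would be biased.

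**What to change.** In section 2.15:

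1. Limit interim tables to IVH and adverse-event counts, including hypothermia. Make no between-arm comparison of temperature or pain.
2. Replace the sentence on discussing results with the team. By-arm interim results stay with the person who already holds unblinded access. The team is told only to continue or to halt, and by-arm safety data are released only if a halt is being considered.
3. State that the primary outcome, margin, sample size and analysis will not be changed on the basis of by-arm interim results.
4. Reconcile sections 2.7, 2.12 and 2.15 on who may see by-arm data. If a second person is to see the counts, name that person as an exception in 2.7 and 2.12, and do not use the final analyst.

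This is a change of wording. The total stays at 70, and no power is lost because no rule uses the temperature look. The price is less open discussion of running safety results in a trial without a monitoring committee. The main investigator also remains unblinded, so the fix narrows the exposure without removing it.
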